## Abstract

**Background:**

Anorexia nervosa (AN) is a mental disorder with grave burdens for affected individuals as well as for the healthcare system. One of the strongest predictors of a poor outcome is a long Duration of Untreated Illness (DUI), which is defined as the time between the onset of the disease and treatment initiation. Reducing the DUI is an important step to optimize care of individuals with AN. In order to achieve this aim, systemic public health interventions are necessary. Objective of this study is to evaluate a systemic public health intervention at Community level aiming to reduce the DUI in individuals with AN.

**Methods/design:**

The intervention includes the establishment of a network of health care professionals within the area of eating disorders (EDs), the development of an internet-based treatment guide, the presentation of informative short-films about EDs in cinemas and a corresponding poster campaign as well as a special outpatient clinic. For the evaluating study a pre-post between-subject design is chosen. The DUI, and the duration until first contact (DUC) with a health care professional, ED pathology as well as comorbidity are assessed before and after the systemic intervention is carried out.

**Discussion:**

The study attempts to provide evidence of the effectiveness of an ED-related systematic public health intervention. Additionally, the study will lead to a better understanding of the DUI, which is essential in order to improve care of individuals with AN.

**Trial registration:**

Current Controlled Trials ISRCTN44979231; Registered 11 November 2011.

## Background

Anorexia Nervosa (AN) is an eating disorder (ED) mainly characterized by a refusal to maintain body weight, an intense fear of weight gain as well as a distortion of body perception. It can have serious adverse consequences on physical as well as psychological health. Common concomitant effects include cardiac arrhythmias, electrolyte imbalances, renal insufficiency, osteoporosis as well as severe infections [1]. In addition, many patients with AN suffer from comorbid psychiatric disorders (e.g. [2-4]) with anxiety and affective disorders being most frequent [5,6].

Compared with other mental disorders, AN occurs relatively seldom with an average prevalence estimated at 0.3% [7]. However, with 0 to 22% the morbidity and mortality rates are among the highest of any mental disease [8,9]. In a 21-year follow-up study 14% of the patients died from reasons directly related to AN [10]. Moreover, in spite of low prevalence rates, AN generates high costs for the health care systems - almost equivalent to those reported for schizophrenia [11].

Due to the various adverse consequences for AN-affected individuals and the healthcare system an early and effective treatment is indispensable. There is evidence for the effectiveness of treatment methods for AN [12]. Nevertheless, estimates show that only half of the AN cases are detected in primary care settings [13] and only one third of the cases detected receive treatment [7]. There can be different reasons for AN- patients to remain untreated. Practitioners might not discover the disorder or patients might decide against a recommended treatment due to the ego-syntonic nature of AN [14].

Even after a successful treatment initiation, there are several factors that may have a negative impact on the course of the disease. The most important predictors of a poor outcome are a low Body-Mass-Index (BMI) as well as severe psychological and social problems [10]. Some studies report that a higher BMI at treatment initiation is the strongest predictor of a successful course [15,16]. Therefore, treatment needs to be initiated before weight loss becomes too severe and protracted [17]. This emphasizes another relevant outcome predictor: the Duration of Untreated Illness (DUI). The DUI describes the time between the onset of an illness and the initiation of treatment. There is evidence for a modest association between DUI and outcome in schizophrenia [18,19] and some indication of an association in mood and anxiety disorders [20,21]. The DUI may also play an important role in AN- patients (e.g. [22,23]). It can be concluded that treatment is more likely to be successful when patients have suffered from AN for a shorter period of time [24]. A review containing six studies from different Western countries found the average DUI to be 1,78 years in patients with AN [25]. This is of great clinical concern as a long duration of AN may be associated with severe complications such as increased mortality [26].

So far, little research has been conducted on factors predicting the DUI in AN. Ackard and colleagues [27] reported the duration of illness to be longer in middle-aged (≥40 years) than in younger women (18–39 years). Healthcare system related aspects influencing the time between symptom onset and treatment utilization are sufficient information about diagnostic and treatment options, availability as well as networking of different care givers [28,29]. Especially general practitioners and pediatricians need to have competence regarding diagnostic of and treatment for EDs to facilitate and accelerate referral into specialist care [30].

There are several interventions and resources available to effectively treat AN [12] which are currently not used to the full extent [7,13]. The reasons for the existing potentials not being exploited fully may be found in individuals as well as systemic structures. Thus, interventions aiming to take this complexity into account have to be multi-faceted as well. In the area of depressions, it has been shown that systemic interventions are able to positively intervene in existing structures. With its four-level intervention program for improving care of patients with depression the “Regensburg Alliance against Depression” succeeded in significantly decreasing suicide rates in Regensburg [31].

### Objectives

The main objective of this project is to minimize the DUI in individuals with AN. In order to achieve the aim of the project, a systemic public health intervention is carried out. It is hypothesized that this intervention decreases the DUI in individuals with AN.

This study is part of the project *psychenet*: *Hamburg network for mental health* funded by the Federal Ministry of Education and Research (BMBF). The purpose of *psychenet* is to work on establishing innovative care models, which aim to make decisive improvements to the prevention, diagnosis and treatment of people with mental illnesses in the Hamburg metropolitan region [32]. *Psychenet* is coordinated by the Cluster Agency Healthcare Hamburg (www.GWHH.de) in collaboration with the University Medical Centre Hamburg-Eppendorf. It consists of a total of eleven sub-projects. Since the network was initiated in 2011, more than 80 scientific and medical institutions, counselling centers, the Senate and the Chamber of Commerce of the Free and Hanseatic City of Hamburg, companies, as well as patients’ and relatives’ associations have been acquired to participate. Sub-project IX (*Health network anorexia and bulimia*) focuses on the improvement of the effectiveness and efficiency of ED-specific care. It aims to optimize the use of available resources as well as the connection of existing structures. The sub-project is divided into two different intervention arms. This article will provide an overview about one intervention arm focusing on treatment initiation in AN patients. An overview about the second intervention arm (a randomized controlled trial on the prevention of EDs in schools) will be described elsewhere.

## Methods

### Study design

For the study purpose, a pre-post between-subject design was chosen. DUI, duration until first contact (DUC), current ED pathology and comorbidity are measured before and after the implementation of the systemic intervention. The pre-data collection takes place between November 2012 and May 2013. Twelve months are planned for the systemic intervention. The post-data collection takes place between May 2014 and November 2014. Figure 1 illustrates the course of the data collection.

**Figure 1 Fig1:**
[figure not shown]
**Course of data collection.** Note. Recruitment for pre- and post-survey occurred within the same institutions offering evidence-based treatment for AN based on the German S3-Guidelines for EDs [35].

### Ethics approval

The study procedure was reviewed and approved by the ethics committee of the Psychotherapist Chamber of Hamburg.

### Study procedures

#### Inclusion and exclusion criteria

In order to participate in the study, a signed informed consent is necessary. Patients below 16 years are required to provide additional informed consent from a parent or legal guardian. Moreover, participants need to have female sex, should be a minimum of ten years old and have a treatment diagnosis of typical or atypical (one criterion absent) AN according to the DSM-IV [33]. Furthermore participants should currently receive their first ED-specific in- or outpatient treatment or be current client of an ED-specific counselling center. Exclusion criteria are insufficient knowledge of the German language as well as substantial organic or psychological complaints preventing participation from the recruiting practitioner’s point of view.

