#### Recruitment

The recruitment is coordinated in cooperation with different ED-specific treatment settings in Hamburg and adjacent areas, i.e. inpatient wards, day clinics, outpatient departments and ED-specific counselling centers. Included institutions offer evidence-based treatment for AN based on the German S3-Guidelines for EDs [34]. A total of eleven clinics, nineteen outpatient departments and four counselling centers are asked to support the project with recruiting participants. A special network meeting is used to inform cooperating practitioners about the study’s content, procedure, and recruitment as well as to provide practitioners with study materials (e.g. written information about the course of recruitment, study design, inclusion and exclusion criteria as well as informed consent forms and questionnaires for participants). During the study, cooperating practitioners regularly receive phone calls to settle any questions and promote adherence.

Cooperating practitioners select eligible participants in line with inclusion and exclusion criteria. Participants found eligible are verbally informed about the aims and procedure of the study and are additionally provided with written material. In case of willingness to participate, participants are asked to sign the informed consent. Practitioners then hand out the questionnaire set, which is described later in this paper. All cooperating practitioners are required to return the completed questionnaires as well as the signed informed consents to the research team. Once all documents are complete, participants are contacted for a structured telephone interview.

The procedure will be identical in the post-survey. Participants who participated in the pre-survey are excluded from participation in the post-survey. Between the two points of data collection the systemic intervention takes place.

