#### Duration until first contact with healthcare system (DUC)

The duration until first contact (DUC) is conceptualized as the number of months between illness onset and the first contact with the healthcare system due to ED-related issues initiated either by the patient or the practitioner. Before starting an ED-specific treatment, patients often have several initial contacts with healthcare professionals or advice centers. The variable DUI can not take these contacts into account because it is defined as the duration until the initiation of a guideline-based treatment. The DUC is meant to improve the understanding of the processes preceding treatment initiation. The questionnaire lists different potential therapeutic settings for AN (inpatient, day-clinic, outpatient, ED-specific counselling) and assesses which of these have been consulted to get information and/or support concerning AN and, in each case, when the first contact took place.

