### Primary outcome

The primary outcome is the DUI, defined as the time in months between the onset of AN and first specific treatment.

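### Eligibility sets no limit on when first treatment began, so the post sample can include patients whose DUI ended before the intervention; and the article conflicts on whether counselling ends the DUI

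*Protocol article*

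**What the plan says.** **Eligibility.** Under Inclusion and exclusion criteria, "participants should currently receive their first ED-specific in- or outpatient treatment or be current client of an ED-specific counselling center". No section adds a condition on the date when treatment started.

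**Outcome.** "The primary outcome is the DUI, defined as the time in months between the onset of AN and first specific treatment".

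**Timing.** Study design: "The pre-data collection takes place between November 2012 and May 2013". The intervention is planned for twelve months and the post-survey runs from May to November 2014. Recruitment places the intervention between the surveys, keeps the procedure the same and adds one exclusion: "Participants who participated in the pre-survey are excluded from participation in the post-survey".

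**Analysis.** Statistical analyses regresses DUI on period of assessment, with age and contact with the intervention as fixed control variables and recruitment setting as a random one. Treatment start date is not in the model.

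**Counselling.** The DUC section says "Before starting an ED-specific treatment, patients often have several initial contacts with healthcare professionals or advice centers", and then "The variable DUI can not take these contacts into account because it is defined as the duration until the initiation of a guideline-based treatment". Recruitment, however, describes the recruiting sites as "different ED-specific treatment settings in Hamburg and adjacent areas, i.e. inpatient wards, day clinics, outpatient departments and ED-specific counselling centers" and says that the included institutions offer evidence-based treatment. The DUC section itself also lists ED-specific counselling among the therapeutic settings.

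**The concern.** DUI is fixed on the day the first treatment starts. An intervention can change it only for patients who start after the intervention has begun. Here the post group is defined by when a patient is surveyed, so it can hold patients whose outcome was settled beforehand. They are analysed as exposed and, if they resemble the pre group, pull the primary contrast towards zero.

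The second issue concerns the end point of the DUI. Eligibility sets counselling beside treatment with an 'or', and the word 'first' belongs only to the treatment limb. If counselling does not end the DUI, a client who has had counselling only has no observed value for the primary outcome. If it does, her value is defined but conflicts with one reading of the DUC section. The intervention publicises routes into care, so the share of patients entering through counselling may differ between periods. An unsettled rule could then affect the comparison.

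**Working it through.** **1. The plan's own figure.** Inputs from Sample size/power calculation: effect size 0.4, difference 4.8 months (so SD = 4.8/0.4 = 12 months), two-sided 5%, power 80%. A two-sample t-test needs 99.08 per group, rounded up to 100, so the stated 100 reproduces. Power at 100 per group is 80.4% (t-test) or 80.7% (normal approximation).

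**2. Who can be an early starter.** With a twelve-month intervention between the surveys, it begins around May 2013. A post patient whose DUI ended before that has been in first treatment for more than about 12 months if recruited in May 2014, or about 18 months if recruited in November 2014. The eligibility rule allows this.

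**3. Dilution.** Let f be the share of the post group that started treatment before the intervention, and assume these patients have the pre group's mean DUI. The expected difference is 4.8 × (1 − f) and the effect size is 0.4 × (1 − f). With 100 per group (t-test):

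| f | Difference (months) | Power |
|---|---|---|
| 0 | 4.80 | 80.4% |
| 5% | 4.56 | 76.2% |
| 10% | 4.32 | 71.7% |
| 20% | 3.84 | 61.5% |
| 30% | 3.36 | 50.4% |

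**4. What f might be.** The article gives no treatment lengths. Assume exponential length with mean m months, a steady caseload, and sampling spread evenly over 12 to 18 months after launch. Then f is the average of exp(−t/m) over that range: f = (m/6) × [exp(−12/m) − exp(−18/m)].

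| Mean m (months) | f | Difference (months) | Power |
|---|---|---|---|
| 3 | 0.8% | 4.8 | 80% |
| 4 | 2.6% | 4.7 | 78% |
| 6 | 9% | 4.4 | 73% |
| 9 | 19% | 3.9 | 62% |
| 12 | 29% | 3.4 | 52% |

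**5. Why these shares are upper limits.** Each patient can enter only once, so the pool is the May 2014 caseload plus six months of new starters. That gives f = m × exp(−12/m)/(m + 6), or 7%, 16% and 25% for means of 6, 9 and 12 months. Early starters who joined the pre-survey are also barred. If half had joined, half of the numerator is removed from both numerator and denominator, leaving about 3-4%, 9% and 14%.

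**6. Counselling.** No arithmetic applies. Three statements bear on the question:
- Eligibility: counselling is an alternative to being in first treatment.
- DUC section: contacts with advice centres come before treatment and do not count towards DUI.
- Recruitment and DUC section: ED-specific counselling is a treatment or therapeutic setting.

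The first two suggest that counselling does not end the DUI, and the third that it does. Counselling centres are 4 of the 34 institutions approached (11 + 19 + 4). That counts sites; the share of patients is not given.

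**The case against.** **The effect may be negligible.** Clinics are 11 of the 34 sites, and inpatient wards and day clinics recruit. If typical treatment lasts 3-4 months, early starters are 1-3% and power hardly moves. This stands. A reader might extend the table to an 18-month mean, where the formula gives 44% and power of 35%, and call the trial badly underpowered. Nothing in the article supports that length, and the formula overstates the share for the reasons in step 5.

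**The bar on pre-survey participants helps.** One might count it as a further flaw because it makes the two sampling frames differ. But it removes some of the very patients at issue, and unequal frames distort DUI only if DUI is related to time in treatment, which the article does not show.

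**Dilution is conditional.** A pull towards zero follows only if early starters resemble the pre group. This also stands.

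**Counselling may be treatment.** A reader might infer that counselling clients have a DUI that has not ended. The documents do not establish that: the advice centres in the DUC section are not identified with the ED-specific centres that recruit, and those centres are described as offering evidence-based treatment. Nor must DUI equal DUC if counselling counts, since an earlier contact with, say, a general practitioner would make DUC shorter. What remains is a conflict over the end point.

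**A fuller plan may deal with it.** Treatment start is already asked about, so an unseen analysis plan could include an analysis by start date. But the article itself states an eligibility rule and an exposure definition that leave the gap open.

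**Adjustment does not close it.** Controlling for contact with the intervention is no substitute, because contact can come after treatment has started.

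**Conclusion.** The point holds in two limited parts.

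First, the eligibility rule and the exposure definition together allow post patients whose DUI ended before the intervention. If they resemble the pre group, each 10% of them costs 0.48 months of the 4.8, and 10% takes power from about 80% to about 72%. The share is unknown. Under exponential treatment length it is about 1-3% for means of 3-4 months and at most 9-29% for means of 6-12 months, less to the extent that early starters took part in the pre-survey. The 12-to-18-month interval assumes a start around May 2013. The section on modules dates the wider network's interventions from 2011 to 2014; an earlier start would make early starters rarer but would expose the pre group.

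Second, the article is inconsistent on whether ED-specific counselling ends the DUI. That leaves the end point of the primary outcome unsettled for counselling clients, whose number is not stated.

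The sample-size arithmetic is not at fault.

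**What to change.** - **Primary DUI set.** Define it by date of first ED-specific treatment. Count post patients only if treatment started after the intervention began, and state that date. Apply the same maximum time in treatment to the pre sample. If the start is May 2013, a limit of 12 months at recruitment in both samples would meet both conditions.
- **Sensitivity analysis.** Report all recruited patients, as the current rule would include them.
- **Counselling.** State one rule, applied in both periods, on whether ED-specific counselling ends the DUI, and bring the eligibility, Recruitment and DUC sections into line. If it does not, keep counselling-only clients in the DUC analysis and leave them out of the DUI regression.

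**Cost.** No new data: Variables and instruments already covers treatment initiation, and the DUC items date the first contact in each setting. Some recruited patients move to the sensitivity set, and 100 per group leaves almost no reserve. The trade is still favourable. If 10% dropped out of each group, 90 per group at an effect size of 0.4 gives 0.4 × √(90/2) − 1.96 = 0.72, or power of about 76.5% (normal approximation). Keeping 10% early starters in the post group gives 72.1% on the same approximation. Limiting post patients to treatment started within May to November 2014 would cost more sample than the problem requires.

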#### Recruitment

The recruitment is coordinated in cooperation with different ED-specific treatment settings in Hamburg and adjacent areas, i.e. inpatient wards, day clinics, outpatient departments and ED-specific counselling centers. Included institutions offer evidence-based treatment for AN based on the German S3-Guidelines for EDs [34]. A total of eleven clinics, nineteen outpatient departments and four counselling centers are asked to support the project with recruiting participants. A special network meeting is used to inform cooperating practitioners about the study’s content, procedure, and recruitment as well as to provide practitioners with study materials (e.g. written information about the course of recruitment, study design, inclusion and exclusion criteria as well as informed consent forms and questionnaires for participants). During the study, cooperating practitioners regularly receive phone calls to settle any questions and promote adherence.

Cooperating practitioners select eligible participants in line with inclusion and exclusion criteria. Participants found eligible are verbally informed about the aims and procedure of the study and are additionally provided with written material. In case of willingness to participate, participants are asked to sign the informed consent. Practitioners then hand out the questionnaire set, which is described later in this paper. All cooperating practitioners are required to return the completed questionnaires as well as the signed informed consents to the research team. Once all documents are complete, participants are contacted for a structured telephone interview.

The procedure will be identical in the post-survey. Participants who participated in the pre-survey are excluded from participation in the post-survey. Between the two points of data collection the systemic intervention takes place.

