In spite of the huge demand for such evaluated interventions, some limitations to this study have to be mentioned: Since this project is a systemic public health intervention, the implementation of a Randomized Controlled Trial (RCT) is not feasible. Therefore, it is problematic to control confounding factors and make causal conclusions. However, this limitation can be attributed to the aims of the project, which leaves no option of implementing a RCT. Due to the complexity of the systemic intervention it is further not realizable to conduct a dismantling investigation. It is assumed that some parts of the intervention act unconsciously. Therefore an entire understanding of the underlying dependencies will not be possible. Moreover, it is decided to exclude male patients from participation - admittedly at the expense of generalization of the results. The reasons for this decision can be found in the low prevalence of AN in males. It has to be noted that there is a lack of standardized measures assessing DUI and DUC. This makes it necessary to develop a new measure for the purposes of the study. Additionally, the variables of interest mainly can only be assessed retrospectively. To counteract a possible distortion, self-reported data is reviewed in the telephone interview. In addition, it has to be considered that a prospective study would not be feasible due to the low prevalence of AN. There are some further limitations concerning the recruitment of the participants. There may be an adherence bias of the cooperating practitioners leading to different participation rates. There may be also a selection bias: Chronified patients with extremely low body weight may display a very long DUI but may be excluded due to their current physical status. The consequence may be an underestimation of the average DUI in the sample.

Since there hasn’t been a comparable intervention in the field of AN, some hypotheses have to stay exploratory. However, the effectiveness of public health interventions in general could be shown already (e.g. [31]). In the field of EDs the *psychenet* intervention and its evaluation will gain new knowledge about the DUI and factors influencing this period. Also, the successful implementation of a systemic intervention in this area will improve the networking of different health care professionals and facilitate patients’ flow into specialist care.

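### Recruiters know the survey period and judge who takes part; if their selection on DUI differs between the surveys it biases the period effect, a consequence the Discussion does not draw

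*Protocol article*

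**What the plan says.** Study design: "For the study purpose, a pre-post between-subject design was chosen". The two groups are two windows: "The pre-data collection takes place between November 2012 and May 2013" and "The post-data collection takes place between May 2014 and November 2014". Under Statistical analyses, the primary test is the regression coefficient for period of assessment, with recruitment setting as a random term and age and contact with the intervention as fixed terms.

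Recruitment: "A special network meeting is used to inform cooperating practitioners about the study’s content, procedure, and recruitment". The materials handed out there cover the study design. Then: "Cooperating practitioners select eligible participants in line with inclusion and exclusion criteria". The same section says that the post-survey procedure will be identical, and the note to Figure 1 says that both surveys recruit in the same institutions.

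Inclusion and exclusion criteria: patients are excluded for "substantial organic or psychological complaints preventing participation from the recruiting practitioner’s point of view".

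Discussion: "There may be an adherence bias of the cooperating practitioners leading to different participation rates". It adds that chronic patients of very low weight may have a very long DUI and be left out, and concludes that the sample's average DUI may be underestimated. For recall distortion it names a countermeasure, the telephone review of self-reports. For selection it names none.

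**The concern.** The primary outcome already exists when a patient is considered for the study, and the treating practitioner will often have a rough idea of how long she has been ill. That practitioner also knows which survey is running. In the post survey the decision comes after twelve months of an intervention aimed at earlier treatment. Selection that is equal in both windows shifts both means alike and mainly limits generalisability. Selection that changes between the windows goes straight into the period coefficient. It can produce a reduction that the intervention did not cause, or hide one that it did.

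The safeguards in the article do not reach this. Identical procedures and the same institutions hold the written rules and the sites constant, but not the way judgement is used. A setting effect and age cannot remove selection on DUI among patients of the same setting and age. The telephone interview checks the dates of enrolled patients only.

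**Working it through.** **Inputs.** From Sample size/power calculation: mean DUI 19 months, target reduction 4.8 months, effect size 0.4, two-sided 5%, power 80%, 100 per group. Derived: SD = 4.8 / 0.4 = 12 months. Assumed, because the documents do not give them: the shape of the DUI distribution and the invitation rates.

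**The plan's own figure.** For a standardised difference of 0.4, the normal approximation gives 99 per group and the t-test 99.08, rounded up to 100. Power at 100 per group is 0.807 (normal) or 0.804 (t). The stated figure reproduces.

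**Sensitivity of the test to a shift.** SE = 12 × √(2/100) = 1.70 months; a difference is significant above 1.96 × 1.70 = 3.3 months. With b the shift caused by period-differential selection and Φ the normal distribution function:

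- no true effect: P(significant) = Φ(b/SE − 1.96) + Φ(−b/SE − 1.96)
- true reduction of 4.8 months with an opposing shift: power ≈ Φ((4.8 − b)/SE − 1.96)

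| b (months) | P(significant), no true effect, nominal 5% | Power for 4.8 months, planned 81% |
|---|---|---|
| 1 | 9% | 61% |
| 2 | 22% | 38% |
| 3 | 42% | 18–19% |

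**What selection gives such a shift.** Take a gamma DUI with mean 19 and SD 12. The longest fifth starts at 27.7 months and has mean 37.9; the other four fifths have mean 14.3. Suppose everyone is invited in the pre survey and only half of the longest fifth in the post survey.

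- Share of that fifth among those invited: 0.2 × 0.5 / (0.8 + 0.2 × 0.5) = 0.111
- Post mean: 0.889 × 14.27 + 0.111 × 37.91 = 16.90
- Shift: 19 − 16.90 = 2.10 months, which is 2.10 / 4.8 = 44% of the target
- Post SD falls to about 10.3, so SE = √((12² + 10.3²)/100) = 1.58
- Chance of a significant false reduction: Φ(2.10/1.58 − 1.96) = Φ(−0.63) ≈ 0.26, against 0.025 without selection

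If 70% of the longest fifth are invited, the shift is 1.21 months and the chance is 11%. A lognormal DUI with the same mean and SD gives shifts of 2.07 and 1.19 months and chances of 26% and 11%.

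**Reverse case.** If the pre survey is the selective one (half of the longest fifth), a true 4.8-month reduction appears as 4.8 − 2.1 = 2.7 months. Power is then Φ(2.7/1.58 − 1.96) ≈ 0.40.

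**The case against.** The Recruitment wording can be read as plain eligibility screening: patients are selected by the criteria, and those found eligible are then informed. On that reading recruiters do not pick among eligible patients. This is fair, but the exclusion that rests on "preventing participation from the recruiting practitioner’s point of view" still leaves judgement, and the Discussion itself expects practitioners to influence participation.

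The limitation is also partly disclosed. The Discussion says that randomisation is not feasible, that causal conclusions are problematic and that selection is possible. What stands is narrower: the consequence for the pre/post contrast is not drawn.

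DUI is hard to measure. Onset is established by questionnaire and interview, and the study had to develop its own measure. A practitioner's impression is therefore rough, and selection on true DUI may be weaker than in the illustration.

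A reader might infer four stronger points that the documents do not support:

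- **All recruiters belong to the network under evaluation.** A network is one intervention component and recruiters are briefed at a network meeting, but membership of every recruiter is not stated.
- **Each site needs to invite only a few patients.** 100 divided by the 34 institutions approached (11 + 19 + 4) is 2.9, but 100 is a required sample and not a quota. With a rare disorder and first treatment only, 2.9 per site could be nearly everyone eligible.
- **No invitation rule or screening log exists.** This is a condensed article, and the full protocol or the written recruitment information may contain both.
- **Selection did differ between the surveys.** Nothing in the article shows this.

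**Conclusion.** The concern holds in a limited form. The group is known to recruiters, recruiters exercise judgement over who takes part, and the article names loss of long-DUI patients as a possible bias. It then draws only the consequence for the average DUI, when the consequence for the primary comparison is the more serious one.

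Under the plan's own mean and implied SD, moderate period-differential selection is worth 1.2 to 2.1 months, a quarter to nearly half of the 4.8-month target. It raises the chance of a false significant reduction from 2.5% to between 11% and 26%. These sizes rest on an assumed distribution and assumed invitation rates; they show what is possible and do not estimate what happens. The point merits a change in the plan but does not invalidate the design.

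**What to change.** 1. In Recruitment, state that in both surveys every consecutive patient who meets the criteria is invited. Each site keeps a short anonymous log (eligible, invited, reason if not, consented, age band, approximate DUI band), collected during the phone calls already planned.
2. Report invitation and consent rates by period, and add a sensitivity analysis of the period effect that allows for selection differing by period.
3. If the pre-survey has closed, do not change the invitation rule for the post-survey alone. That would break the identical procedure and could create the very bias at issue. Keep the procedure as it was, log the post-survey, obtain retrospective pre-survey counts of eligible patients where sites can give them, and treat the comparison as a sensitivity analysis only.
4. In the Discussion, state that selection differing by period can create or mask the primary effect.

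If the full protocol already contains a log and an invitation rule, only the sensitivity analysis, the reporting by period and the Discussion sentence remain to be added.

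Cost: slightly more work for practitioners, plus one further analysis. DUI bands for patients who do not take part are only approximate, so the analysis can indicate the direction and rough size of a bias but cannot correct it exactly.
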